**2.3.9 Statistical approach**

The primary analysis population is the full analysis set, which, following intention-to treat (ITT) principles, includes all randomized patients.

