### **2.2.3. Patient population, inclusion, and exclusion criteria**

Residents on the medical wards will be the primary level of randomization. We have no exclusion criteria for physicians except if they refuse participation. Outcomes will be assessed in patients treated by these physicians. Any adult (>18 years) patient that is admitted for in-hospital care will be eligible. There will be no exclusion based on the type of illness, comorbidity or severity of illness in order to include a representative population of patients in Swiss hospitals. We will exclude patients unable to complete questionnaires or unable to follow code status discussions due to (1) intoxication, (2) paracsis; (3) serious psychiatric conditions (e.g., psychosis, depression with suicidal tendency, stupor), (4) cognitive impairment (e.g. dementia, delirium). Also, patients prior included in this study (i.e., patients who are hospitalized for the second time) are not eligible. Patients, in whom resuscitation attempts would be futile, will not be included in this study.

Recently Ebell et al developed the GO-FAR score, a clinical risk score to predict the estimated likelihood of neurologically intact survival of patients after in-hospital resuscitation[41]. The authors developed a multivariate prediction model based on 51`240 patients who experienced in-hospital cardiac arrest and calculated cut-off scores indicating likelihood of functional survival. The two lowest categories represent very low (<1%) and low (1-3%) likelihood of survival. It has therefore been suggested that these patients should be considered futile regarding CPR attempts [42]. Another tool to assess whether patients are at increased risk for poor outcome is the Clinical Frailty Scale[43]. This 9-category scale combines cognitive and physical aspects of frailty such as comorbidity, cognitive impairment, and disability. Research has shown that the scale, which is increasingly used in routine screening of older patients, predicts short-term mortality[44, 45]. However, the prevalence of futility in hospitalized patients upon admission assessed through the GO-FAR score and the Clinical Frailty Scale has not been systematically investigated.

According to the literature, we will define futility as a GO-FAR score  $\geq 14$  or patients in categories 7-9 in the Clinical frailty scale.

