#### **2.2.5. Study flow**

Code status discussions are usually conducted by the treating residents on the ward. Residents that agree to participate will be randomized into the intervention or control group with a 1:1 allocation (see Figure 1). Randomization will be done by a pre-specified, computer-generated, web-based randomization scheme (block randomization with variables sizes of 4 to 6). The randomization will be stratified for the trial site. The CTU Basel is responsible for the integrity of the randomization procedures and randomization will be electronically integrated in the SecuTrial® website, where also all data collection for this trial is done.

The study will be conducted for admissions from Monday to Friday. Admission on medical wards normally takes place between 8:00 am and 4:00 pm. Residents that participate in our study will report all new admissions to our study team. Additionally, we will check the hospital's database and the hospital's bed managers will provide us with a list of planned hospitalizations one day in advance. A member of our study team will then check whether the new patient is eligible for trial inclusion.

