#### **Figure 1. Study flow**

[figure not shown]

Baseline data will be entered into a centralized web-based study software (SecuTrial®) provided by the Clinical Trial Unit (CTU). The following baseline-data will be recorded for each patient:

- Socio-demographics (e.g., age, gender, socio-economic status, religion,)
- Health-related quality of life defined by EQ-5D (EuroQol)[46]
- Medical situation (i.e., complete list of main diagnosis and comorbidities)

To enable blinding of patients and physicians regarding the intervention and main endpoint of our trial, we will not share any detailed information, but ask for their participation in a trial comparing two different communication strategies on the quality of code status discussions. Yet, blinding of the study coordinator is not feasible. After code status discussion, a member of our research team will interview patients and residents separately. Using a structured questionnaire, patient outcomes and perceived quality of care as defined below (2.2.8. primary and secondary endpoints) will be assessed. In addition, the physician's perception of the code status discussion will be examined using a structured questionnaire.

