## *Study protocol and statistical analysis plan*

We will use cluster specific methods because residents rather than patients are randomized, and we expected that variance in how patients are managed would be partly explained by the resident. We will further account for the level of the participating center (hospital), as DNR discussions may vary according to study center. For each of the outcome measures we will test the null hypothesis that the likelihood of the outcome is the same in both study groups after accounting for some baseline characteristics (i.e., age, gender, main medical diagnosis). We will use hierarchical logistic regression to test for an effect of the intervention on any binary outcome measures and linear regression for any continuous outcome measure.

All analyses will be conducted using Stata. All analyses were performed using STATA 15.1 (Stata Corp, College Station, TX). For all analyses, we accept a type I error rate of  $\alpha = 5\%$ .

The design of our study and statistical approach was developed in close collaboration with statisticians and epidemiologists of the Clinical Trial Unit (CTU) of the University Hospital Basel.

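### The primary analysis set is defined by randomised patients in a trial that randomises residents, and patient eligibility is not required to be masked or fixed before the discussion

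*Combined protocol and SAP*

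**What the plan says.** Section 2.3.9 (Statistical approach) defines the primary population: "The primary analysis population is the full analysis set, which, following intention-to treat (ITT) principles, includes all randomized patients". The same section then justifies cluster methods on the ground that "residents rather than patients are randomized". Section 2.2.3 agrees: "Residents on the medical wards will be the primary level of randomization". So does Section 2.2.5: "Residents that agree to participate will be randomized into the intervention or control group with a 1:1 allocation".

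The order of events comes from Sections 2.2.5 and 2.2.6. Residents are allocated and attend an arm-specific workshop before they begin code status discussions. They then report new admissions, and the team also consults the hospital database and the bed managers' list of planned admissions. Next, "A member of our study team will then check whether the new patient is eligible for trial inclusion". On masking, the text with Figure 1 says "Yet, blinding of the study coordinator is not feasible". It does not mention the person who checks eligibility.

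Section 2.2.3 sets the exclusions: "We will exclude patients unable to complete questionnaires or unable to follow code status discussions due to" four named causes, among them intoxication, serious psychiatric conditions and cognitive impairment. Futile patients are also excluded, defined as GO-FAR 14 or more or Clinical Frailty Scale 7 to 9.

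**The concern.** There are two linked problems. First, the definition cannot be applied as worded. Read literally it contains nobody. Read charitably, as patients of randomised residents, it still does not say what makes a patient count: admission, a passed eligibility check, a discussion held, or a status documented.

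Second, the intention-to-treat label protects the comparison of residents, not the selection of patients under them. When patients enter after their cluster is allocated, the arms are comparable only if entry works the same way in both. Several criteria involve judgement: whether a patient can follow the discussion, whether cognition is impaired, and whether frailty is category 6 or 7. Frailty and cognition plausibly also influence the choice of DNR, which is the primary endpoint. In addition, under Section 2.4 (Parallel study), futile patients leave the main trial for the parallel project, where only intervention residents receive futility teaching and a checklist. Classification at that border could therefore differ by arm.

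**Working it through.** **Plan's own figure.** Inputs from Section 2.3.10: DNR 30% against 45%, power 80%, alpha 0.05 (two-sided assumed, as sidedness is not stated), ICC 0.5, 15 patients per resident. The two-proportion formula without continuity correction gives 163 patients per arm. The design effect is 1 + (15 − 1) × 0.5 = 8. Then 163 × 8 / 15 = 86.9, so 87 residents per arm, 174 in all, and 174 × 15 = 2610 patients. The stated size reproduces exactly, and nothing in this point changes it.

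**Illustration of what unequal entry could do.** These inputs are assumptions and are not in the documents: no true effect; DNR 30% in the comparison arm; DNR 70% in borderline-frail patients; the share of such patients in one arm shifted by s = 5 or 10 points; no covariate adjustment.

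- Shifted arm: p = 0.30 × (1 − s) + 0.70 × s. For s = 0.05, p = 0.285 + 0.035 = 0.32, a bias of 2 points. For s = 0.10, p = 0.27 + 0.07 = 0.34, a bias of 4 points. For s = 0 the bias is zero.
- Standard error: SE = √[(0.30 × 0.70 + p(1 − p)) × DEFF / n], with n = 87 × 15 = 1305 per arm and DEFF = 1 + 14 × ICC.
- Type I error: P(|Z + bias/SE| > 1.96).

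At ICC 0.5 (DEFF 8):
- s = 0.05: SE = √(0.4276 × 8 / 1305) = 0.0512; bias/SE = 0.39; type I error 6.8%.
- s = 0.10: SE = √(0.4344 × 8 / 1305) = 0.0516; bias/SE = 0.78; type I error 12.1%.

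**If the ICC is lower.** Section 2.3.10 plans to re-estimate the ICC after 30 residents and adjust the sample size. For 80% power:
- ICC 0.10: 163 × 2.4 / 15 = 26.1, so 27 per arm, 54 residents.
- ICC 0.05: 163 × 1.7 / 15 = 18.5, so 19 per arm, 38 residents.

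| ICC | Residents | Type I error, s = 0.05 | Type I error, s = 0.10 |
|---|---|---|---|
| 0.5 | 174 | 6.8% | 12.1% |
| 0.10 | 54 (resized) | 6.8% | 12.4% |
| 0.05 | 38 (resized) | 6.8% | 12.3% |
| 0.10 | 174 (kept) | 11.0% | 29.3% |
| 0.05 | 174 (kept) | 13.5% | 39.0% |

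The bias in points is the same in every row. Only its size relative to the standard error changes.

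**A second mechanism as a cross-check.** Suppose 10% of eligible patients in one arm are not entered and their DNR rate is q. The observed rate is (0.30 − 0.10q)/0.90. For q = 0 this is 33.3% and for q = 60% it is 26.7%, shifts of +3.3 and −3.3 points. At ICC 0.5 the rejection rate is about 10% in either case. For q = 30% there is no shift.

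**The case against.** The plan has real safeguards. The Summary specifies consecutive patients. The database and bed-manager lists in Section 2.2.5 limit missed admissions. Futility has stated cut-offs, and inability to follow the discussion is tied to named causes. Section 2.3.9 adjusts for age, gender and main diagnosis. All of this lowers the risk. It does not stop an admission on the list from being judged ineligible more readily in one arm, and the adjustment does not include frailty or cognition.

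A reader might infer four stronger things that the documents do not support.

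- That screening is done with knowledge of the arm. Only the study coordinator is said to be unmasked; the screener's masking is not addressed. Section 2.2.6 separates workshop staff from later contacts to improve blinding, though it also has the trainer accompany residents to at least three discussions. Figure 1 is not available in the text reviewed and may show more about the order of steps.
- That patients who decline the questionnaires may drop out of the primary analysis. Section 2.2.4 waives patient consent for code status, and Section 2.2.8 takes the endpoint from the chart.
- That type I error would reach 29% or 39%. Those values need a low ICC with all 174 residents kept, contrary to the resizing described in Section 2.3.10.
- That bias will occur. What is shown is missing protection.

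**Conclusion.** The point stands as a defect in the primary analysis definition together with a gap in design protection. The definition contradicts Sections 2.2.3 and 2.2.5 and the rest of Section 2.3.9. Nothing in the plan requires masked eligibility or eligibility settled before the discussion.

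The size is illustrative: 2 or 4 points of bias and type I error of about 7% or 12%, at ICC 0.5 or after resizing. It rests on the assumed 70% DNR rate, the assumed 5- or 10-point shift and no covariate adjustment. It falls to zero if entry is equal in the two arms. For comparison, the planned effect is 15 points. The matter should be settled before the analysis, because screening decisions that were never logged cannot be reconstructed.

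**What to change.** Replace the definition with: all eligible patients admitted under a randomised resident during that resident's 3-week window, analysed in the resident's allocated arm, whether or not the discussion took place or questionnaires were consented to. Then add:

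- Eligibility is assessed from the hospital admission lists and recorded with a time stamp before the discussion, by an existing team member who is not told the arm.
- No exclusion is allowed once the discussion has started.
- Screened, excluded and included counts, with reasons, are reported by arm.
- Undocumented code status is handled by prespecified sensitivity analyses. Counting every undocumented status as not DNR should not be the single fixed rule: the intervention checklist itself tells residents to document, so documentation may be more complete in that arm and the rule could create a difference.

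The cost is SAP wording, a screening log and some logistics with existing staff. Masking will be imperfect, since the screener still receives reports from trained residents. A few patients who prove unable to follow the discussion will remain in and slightly dilute the effect.

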## *Study protocol and statistical analysis plan*

We will use cluster specific methods because residents rather than patients are randomized, and we expected that variance in how patients are managed would be partly explained by the resident. We will further account for the level of the participating center (hospital), as DNR discussions may vary according to study center. For each of the outcome measures we will test the null hypothesis that the likelihood of the outcome is the same in both study groups after accounting for some baseline characteristics (i.e., age, gender, main medical diagnosis). We will use hierarchical logistic regression to test for an effect of the intervention on any binary outcome measures and linear regression for any continuous outcome measure.

All analyses will be conducted using Stata. All analyses were performed using STATA 15.1 (Stata Corp, College Station, TX). For all analyses, we accept a type I error rate of  $\alpha = 5\%$ .

The design of our study and statistical approach was developed in close collaboration with statisticians and epidemiologists of the Clinical Trial Unit (CTU) of the University Hospital Basel.

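### The planned model leaves out the GO-FAR score and the Clinical Frailty Scale, although the futility exclusion requires both; storing and adjusting for them is a cheap improvement

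*Combined protocol and SAP*

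**What the plan says.** Section 2.3.9 (Statistical approach) tests each outcome "after accounting for some baseline characteristics (i.e., age, gender, main medical diagnosis", and the bracket closes there, so the list is complete as written. For the primary outcome the model is fixed: "We will use hierarchical logistic regression to test for an effect of the intervention on any binary outcome measures". Hospital is covered too: "We will further account for the level of the participating center (hospital), as DNR discussions may vary according to study center".

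Section 2.2.3 states: "Patients, in whom resuscitation attempts would be futile, will not be included in this study". The definition reads "we will define futility as a GO-FAR score" of at least 14, or "patients in categories 7-9 in the Clinical frailty scale".

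Under section 2.2.5 residents are randomised first. They then report new admissions, and "A member of our study team will then check whether the new patient is eligible for trial inclusion". The baseline data listed after Figure 1 are socio-demographics, EQ-5D, and main diagnosis with comorbidities; neither score is named. The same section concedes that "blinding of the study coordinator is not feasible".

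Section 2.3.10 plans 174 residents with 15 patients each (2610 patients) for 30% versus 45% DNR, 80% power, alpha 0.05 and an ICC of 0.5. It calls that ICC conservative and will adjust the sample size to the ICC estimated, blinded, from the first 30 residents.

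**The concern.** An exclusion that applies when either scale is above its threshold can be cleared only by checking both. Each included patient must therefore have been judged on two prognostic measures, yet the plan neither lists them as baseline data nor uses them in the analysis.

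This matters more than it would in an individually randomised trial, because patients are recruited after allocation. Hospital database checks and bed-manager lists limit under-reporting of admissions, but they do not show whether the futility rule was applied alike in both arms. The same thresholds divide patients between the main trial and the parallel project (section 2.4), and only intervention residents receive the futility teaching and checklist. If classification near a threshold depended on arm, the two main-trial populations would differ, and without stored scores nobody could tell.

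At stake are a check on differential selection and some precision.

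**Working it through.** **Inputs.** From section 2.3.10: p1 = 0.30, p2 = 0.45, m = 15 patients per resident, ICC = 0.5, power 80%, alpha 0.05 (taken as two-sided, which reproduces the plan's figure). Assumed: the two scores explain R2 = 10-30% of within-resident variance beyond age, gender and diagnosis. The documents give no such figure.

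**1. The plan's figure.** With pooled variance and no continuity correction:

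n = [1.960 × √(2 × 0.375 × 0.625) + 0.842 × √(0.30 × 0.70 + 0.45 × 0.55)]² / 0.15² = 162.3, so 163 per arm.

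The design effect is 1 + 14 × 0.5 = 8, and 163 × 8 = 1304 per arm. Dividing by 15 gives 87 residents per arm: 174 residents and 2610 patients, as stated. Power is 80.2%.

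**2. Variance with the scores added.** The variance of a resident's mean is proportional to V0 = ICC + (1 − ICC)/m. If the scores explain only within-resident variance, it becomes V1 = ICC + (1 − ICC)(1 − R2)/m. This is a linear approximation to the planned logistic model. Residents needed per arm are 163 × V0, rounded up.

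| ICC | V0 | V1 (R2 10%; 30%) | Fall in variance | Residents by the plan's formula (patients) |
|---|---|---|---|---|
| 0.5 | 0.5333 | 0.5300; 0.5233 | 0.6%; 1.9% | 174 (2610) |
| 0.10 | 0.1600 | 0.1540; 0.1420 | 3.8%; 11.3% | 54 (810) |
| 0.05 | 0.1133 | 0.1070; 0.0943 | 5.6%; 16.8% | 38 (570) |

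**3. Power.** The effective size per arm is residents per arm divided by V0 or V1, put into the formula of step 1 solved for power.

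- ICC 0.5, 174 residents: 80.2% rises to 80.4-80.9%.
- ICC 0.10, still 174 residents: already above 99% unadjusted. Resized to 54: 81.5% rises to 83.0-85.9%.
- ICC 0.05, resized to 38: 81.3% rises to 83.4-87.8%.
- Upper bound at ICC 0.5, if the scores explained the same 10-30% of between-resident variance as well: 84-92%.

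**4. Chance imbalance.** The SD of a standardised covariate difference between arms is √[(2/N per arm) × (1 + 14ρ)]. With covariate ICC ρ from 0 to 0.1 (assumed), it is 0.04-0.06 at 1305 per arm and 0.08-0.13 at 285 per arm (570 patients).

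**5. Effect on the estimand.** The planned rates give a marginal odds ratio of (0.45/0.55)/(0.30/0.70) = 1.91. Conditioning on a further covariate with a log odds ratio of 0.3 to 1.0 per SD (assumed) turns this into a conditional odds ratio of 1.93 to 2.17. The covariate set is therefore part of what is estimated.

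**The case against.** The strongest reply is that nothing is wrong. Covariates are pre-specified, the model is hierarchical, hospital is accounted for, and the randomised comparison needs no further covariates. That stands. At the planned ICC the precision gain is negligible, and at lower ICCs the full 174 residents already give ample power. That stands too, unless the blinded review reduces the number of residents, which is the purpose of that review if the ICC proves low.

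A second reply is that the remedy carries its own risk. Frailty rating is partly a judgement and is made after allocation, so a rater who knows the arm could bring allocation into the covariate. This is a fair limit on how frailty is used. It does not argue against storing it.

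A reader might infer more than the documents support:

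- **That the scores are known to drive DNR choice.** Section 2.2.3 links GO-FAR to neurologically intact survival and the frailty scale to short-term mortality. No figure links either to the choices of non-futile patients, and the exclusion removes the top of both scales, which would weaken any association. A link is plausible but not shown.
- **That main diagnosis carries little prognostic information.** Section 2.4 says that cancer, renal failure, sepsis and pulmonary disease are associated with worse outcomes. The gap is only that no grouping of diagnoses is defined for an all-comers population.
- **That the unadjusted result would be materially biased.** One could posit 70% DNR in frail and 30% in other patients, with a 10-point imbalance in the frail share, giving 0.10 × 0.40 = 4 points. With those rates the control rate exceeds the planned 30% as soon as any patient is frail. Chance would hardly produce the imbalance: with an assumed 30% frail share and 1305 per arm, the SE of the difference is 1.8-2.8 points (covariate ICC 0 to 0.1), so 10 points is 3.6-5.6 SEs. It would need systematic selection, for which the documents give opportunity but no evidence.

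**Conclusion.** The point holds as a recommended improvement of minor to moderate weight. The covariate list is closed and omits two measures that the plan's own exclusion rule requires. They are not in the baseline list, so they may be used at screening and then lost. The main benefit is a check on differential selection in a trial that enrols patients after allocation; adjustment cannot correct selection on unmeasured factors.

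The precision benefit is a 1-2% fall in variance at ICC 0.5, 4-11% at 0.10 and 6-17% at 0.05. It rests on the assumed R2 of 10-30% beyond the planned covariates and on the linear approximation. It becomes material only if the sample size is cut after the ICC review. The omission does not invalidate the primary comparison.

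**What to change.** 1. Add the GO-FAR score and the Clinical Frailty Scale category to the baseline data in section 2.2.5. Store the values, not just whether a threshold was passed, for every included patient. State that they are rated before the code status discussion and, where possible, by someone blind to the resident's arm.
2. Report both scores by arm as a check on differential selection.
3. In section 2.3.9, extend the list to age, gender, GO-FAR score, Clinical Frailty Scale category and main diagnosis in pre-defined broad groups, and state the form in which each enters the model. Centre needs no change. If frailty cannot be rated blind to arm, leave it out of the primary model and adjust for it in a pre-specified sensitivity analysis.
4. State that the odds ratio is conditional on this covariate set, and fix the set before unblinding.

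The cost is two eCRF fields, a grouping table for diagnoses and a few sentences in the plan. Scores not stored at screening may not be recoverable later, so the fields should come first. The waiver of patient consent in section 2.2.4 is described for code status, so the sponsor should confirm that storing the scores is covered.

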## **1. Summary of the research plan**

**Background:** A patients' decision regarding "Do Not Resuscitate" (DNR) code status, which is a legal order to withhold cardiopulmonary resuscitation (CPR) or advanced cardiac life support in respect of a patient's wish in case of a cardiac arrest or respiratory failure, has important medical and socioeconomic consequences. Yet, hospitalized patients often have insufficient information about expected outcomes from resuscitation measures. Research shows that <20% of in-hospital patients, who require CPR survive and subsequently many have permanent brain damage or disability. Although challenging in clinical routine, sharing information about expected prognosis with patients is a prerequisite for informed decision-making. In a recent hospital-based survey we found that DNR discussions are often insufficient with physicians not actively involving patients in the decision-making process, but relying decisions on the presumed preferences without in-depth discussions of patients' choices and consequences.

**General aim:** This trial is designed to investigate whether checklist-guided shared decision-making including decision aids and communication of expected outcome influences patients' decision regarding DNR code status, and at the same time, improves decision-making quality as judged by patient's decisional comfort, patient knowledge and involvement in decision-making and patient satisfaction.

**Patient population:** Consecutive adult medical patients admitted for in-hospital care, independent of medical diagnosis are eligible. Patients unable to complete questionnaires or unable to follow code status discussions (e.g., due to cognitive impairment such as dementia or delirium) and patients in whom resuscitation efforts are deemed futile are excluded.

**Methods:** multicenter, cluster randomized controlled trial involving six Swiss teaching hospitals.

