### **2.3.10 Power and sample size considerations**

For sample size calculation, we consider the intra-cluster correlation coefficient, the number of events, the expected effect, and the power of the study. Based on pilot data in this patient population, we expect that 30% of patients in the usual care control will have a DNR code status, which will increase to 45% in the intervention group. We plan to include 174 residents (cluster) with a mean of 5 eligible patients per week over a 3-week period (total of 15 patients per cluster) in the five participating centers over a total study time of 2 years. Based on these assumptions, we will include 2610 patients among 174 residents, which will give this study an 80% power at a 0.05 alpha error with an inter-cluster correlation of 0.5. Because the inter-cluster correlation in this setting is unknown, we used a conservative estimate above, but plan to possibly adjust the sample size based on a blinded interim analysis after data of 30 residents (cluster) is collected. In this interim analysis, we estimate the intraclass correlation of code status decisions, i.e., how much the code status decisions are cluster-dependent. Based on this estimation of intraclass correlation, we will adjust the total required sample size.

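### Every outcome is tested at 5% with no testing order and no rule for which result supports the quality half of the joint aim, so four to seven outcomes could carry that claim

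*Combined protocol and SAP*

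**What the plan says.** **Testing rule (2.3.9).** "For each of the outcome measures we will test the null hypothesis" of equal likelihood in both groups, and "For all analyses, we accept a type I error rate of" 5%. Neither 2.3.9 nor 2.3.10 contains a test sequence, a gatekeeping rule, an adjustment, or a statement that any outcome is exploratory.

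**Aim (Section 1, General aim; 2.2.1).** The trial asks whether the intervention influences the DNR decision "and at the same time, improves decision-making quality". Both places judge quality by four domains: decisional comfort, knowledge, involvement in the decision, and satisfaction.

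**Ranking of outcomes (2.2.8; Section 1, Endpoints).** There is one primary outcome (DNR frequency), one key secondary endpoint (Decisional Conflict Scale), and a list of additional secondary endpoints. The summary equates the key secondary with the quality of decision-making, as shown by decisional comfort.

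**Sample size (2.3.10).** It concerns the primary outcome only: 174 residents and 2610 patients, "which will give this study an 80% power at a 0.05 alpha error with an inter-cluster correlation of 0.5".

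**The concern.** The second half of the aim has no success rule. The summary's endpoint paragraph ties quality to the Decisional Conflict Scale, while the aim spreads it over four domains. Section 2.3.9 does not choose between the two. Suppose the primary is significant, the Decisional Conflict Scale is null, and one satisfaction rating reaches p < 0.05. Nothing in the plan would stop the report from concluding that decision quality improved. Calling one secondary endpoint key gives no protection, because that word has no effect on how the tests are run or read.

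What is at stake is the credibility of the statement that the intervention changes DNR choice and improves decision quality too. The finding on DNR frequency itself is not at stake.

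**Working it through.** **1. Reproduce the plan's own figure.** The inputs from 2.3.10 are 30% against 45% DNR, 15 patients per resident, intra-cluster correlation 0.5, 80% power and alpha 0.05. Allocation is 1:1 (2.2.5).

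- Per arm without clustering (normal approximation, pooled variance under the null, two-sided, no continuity correction): n = [1.960·√(2·0.375·0.625) + 0.842·√(0.30·0.70 + 0.45·0.55)]² / 0.15², rounded up to 163.
- Design effect: 1 + (15 − 1)·0.5 = 8.
- 163·8 = 1304 patients per arm; 1304/15 rounds up to 87 residents per arm.
- Total: 174 residents and 174·15 = 2610 patients. Power at this size is 80.2%.

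The plan's figures reproduce exactly. The sidedness of alpha is not stated. A one-sided test would give 138 residents, so the plan evidently used two-sided 5% for the primary alone.

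**2. Count the outcomes that can speak to quality (2.2.8 read against the four domains).**

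- Decisional comfort: 1 (Decisional Conflict Scale)
- Knowledge: 1 (score 0 to 6)
- Involvement: 1 (SDM-Q-9)
- Satisfaction: 4 visual analogue ratings, or 1 if only overall satisfaction is used

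This makes 1 + 1 + 1 + 4 = 7 tests, or 4 with one satisfaction item.

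**3. Chance of at least one p < 0.05 when the intervention has no effect on quality.** Under independence this is 1 − 0.95^m. Counting only results that favour the intervention, it is 1 − 0.975^m. The correlated figures come from simulation (200,000 draws) with an assumed common correlation of 0.3 to 0.7, since the documents give none.

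| Outcomes that may carry the claim | Independent, either direction | Independent, favourable | Correlated 0.3 to 0.7, either direction | Correlated 0.3 to 0.7, favourable |
|---|---|---|---|---|
| Decisional Conflict Scale only | 5% | 2.5% | 5% | 2.5% |
| 4 | 18.5% | 9.6% | 17.4% to 13.1% | 8.7% to 6.5% |
| 7 | 30.2% | 16.2% | 27.2% to 17.7% | 13.9% to 8.8% |

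**4. False joint claim.** Suppose DNR frequency truly changes as planned (power 0.802), quality does not, and the quality tests are independent of the primary.

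- Any of 7: 0.802·0.302 = 24% (favourable only: 0.802·0.162 = 13%)
- Any of 4: 0.802·0.185 = 15% (favourable only: 0.802·0.096 = 8%)
- Decisional Conflict Scale only: 0.802·0.05 = 4% (favourable only: 0.802·0.025 = 2%)

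**5. Effect of the remedy on the primary.** In a fixed sequence the primary keeps the full 5%, so 174 residents and 80.2% power stand. The familywise error over the primary and the key secondary is 5%. Splitting alpha instead (0.025 each) would cut primary power to 71.3%, or require 212 residents (212·15 = 3180 patients).

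**The case against.** The other side has four fair arguments.

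- **The plan does have a hierarchy.** It names one primary and one key secondary, and its summary links quality to the latter. This stands. What is missing is a testing order, not a ranking.
- **A joint claim needs no adjustment.** If the conclusion requires both the primary and the Decisional Conflict Scale at 5%, there is no inflation. This is also correct. Inflation arises only if another quality outcome may substitute. The plan does not say that it may, but it does not exclude it, and the four-domain wording of the aim invites it.
- **Unadjusted secondary outcomes are common.** That is acceptable when they are labelled exploratory. Here they are hypothesis tests at 5%, and some are named components of the aim.
- **Gating the Decisional Conflict Scale on DNR frequency is debatable.** Section 2.2.8 chose the scale because patients put weight on being able to make a reasonable decision, and quality could improve with no shift in DNR choice. This is a real cost, but a small one for the aim as written, because a joint conclusion already needs the primary.

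A reader might also infer that all the secondary outcomes in 2.2.8 could supply the quality half. There are 1 + 1 + 1 + 4 + 4 + 3 + 1 + 4 = 19 (Decisional Conflict Scale, knowledge, involvement, fears, satisfaction, physician ratings, surprise question, 30-day outcomes), so the risk would be 1 − 0.95^19 = 62%. The documents do not support this. Length of stay, ICU admission, re-admission, mortality, the surprise question and the physician ratings lie outside the four domains. The fear items serve a different hypothesis, stated at the end of 2.1: that fear will not increase. The 62% also counts significant worsening as improvement.

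**Conclusion.** The point holds in a limited form. Section 2.3.9 applies 5% to every outcome without a testing order, multiplicity handling or a rule for the quality conclusion, so the key secondary is key in name only. If any outcome in the four quality domains may carry the claim, the error rate is 18.5% to 30.2% (9.6% to 16.2% favourable) instead of 5% (2.5%).

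These figures assume that no quality outcome is truly affected and that the tests are independent. Positive correlation, which is likely among ratings of the same conversation, lowers them but leaves them well above the single-test level over the range examined. The false-joint-claim figures further assume independence from the primary and power as planned.

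It would be wrong to infer that the primary result is compromised: there is one primary outcome, tested once at 5%, and its sample size reproduces. The parallel study on futility has its own outcomes and is not counted here. This is a cheap improvement to the plan, not a threat to its main comparison.

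**What to change.** Add to 2.3.9, before the data are compared by group:

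- DNR frequency is tested at two-sided 5%.
- The Decisional Conflict Scale is tested at two-sided 5% only if the primary is significant.
- The joint conclusion (DNR choice changes and decision quality improves) requires both tests to be significant, with the Decisional Conflict Scale favouring the intervention.
- All other secondary outcomes (knowledge, SDM-Q-9, satisfaction, fears, physician ratings, surprise question, 30-day outcomes) are reported as estimates with 95% confidence intervals, labelled exploratory and supportive.

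Then align the aim in Section 1 and 2.2.1. As worded, it puts knowledge, involvement and satisfaction on the same footing as decisional comfort. It should name the Decisional Conflict Scale as the confirmatory measure of quality and the other three domains as supportive. Without this step the SAP and the aim would disagree.

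The cost is wording in the SAP and in the aim. No patients, residents or primary alpha are given up. The downside is that a favourable Decisional Conflict Scale result could not be claimed as confirmatory if DNR frequency does not differ.
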